### 5.1. Visit 1 (Day -7~0) – Screening

At Visit 1, informed consent must be obtained prior to performing any procedures related to the study and after the healthy volunteer has received sufficient information about the study, the opportunity to ask any questions, and consider the options.

Subjects who have been screened should be listed on the Screening Log. Moreover, all screening procedures conducted and the primary reason for not continuing must be documented in the CRF, but no data will be entered into the database for all screened subjects who do not meet criteria for entering the study. No CRF other than the screening part should be completed for these subjects. The following study procedures will be conducted for screening assessments.

- (1) Record date of informed consent signed. Document in the subject's medical chart that he/she is participating in this study, informed consent has been obtained and a copy of the consent has been given to the subject.
- (2) Check inclusion/exclusion criteria.
- (3) Collect the demographic data, including date of birth, age, gender and ethnicity.
- (4) Collect relevant medical history and concurrent diseases. Where possible, diagnoses and not symptoms should be recorded.
- (5) Conduct a complete physical examination including the measurement of weight and height. Measure and record the oral temperature.

- (6) Collect urine samples for pregnancy test (in females of childbearing potential only).
- (7) Collect approximately 8 ml of whole blood sample for following local laboratory tests.
  - Hematological tests: CBC, including Hb, Hct, RBC count, WBC count, WBC differential and platelet count.
  - Biochemistry tests: ALT, AST,  $\gamma$ GT, alkaline phosphatase, total bilirubin, total protein, albumin, BUN, creatinine, uric acid, total cholesterol, triglyceride and glucose (fasting).
- (8) Review prior and concomitant medications. All medications, including vaccine(s), taken during the 30-day period before vaccination should be recorded.

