## 5.2. Visit 2 (Day 0) – 1st vaccination

The first dose of study vaccine should be administrated within 1 week after the screening visit. All subjects should complete the following study procedures **prior to vaccination**.

- (1) Check inclusion/exclusion criteria.
- (2) Check withdrawal criteria.
- (3) Conduct randomization of the qualified participant into one of the following dosing groups.
  - **Group A05:** 0.25 ml per dose (5  $\mu$ g total protein + adjuvant 150  $\mu$ g AlPO4)
  - **Group B10:** 0.5 ml per dose (10  $\mu$ g total protein + adjuvant 300  $\mu$ g AlPO4)
- (4) Conduct a complete physical examination with an exception of body height. Measure and record the oral temperature.
- (5) Collect urine samples for pregnancy test (in females of childbearing potential only).
- (6) Collect approximately 7 ml of whole blood sample for following central laboratory tests.
  - Immunogenicity tests: IgG and neutralizing antibody titers, and epitope mapping.

The study vaccine will be administrated intramuscularly (i.m.) in the deltoid of the non-dominant arm. **After vaccination:**

- (1) Observe closely during vaccination and at least 2 hours after vaccine administration. An appropriate medical treatment should be readily available in case of a rare anaphylactic reaction following vaccination.
- (2) Conduct a telephone follow-up 7 days after vaccine administration.
- (3) Dispense thermometer and self-evaluation diary card. Instruct the subjects to monitor body temperature and complete the diary correctly.  
Any solicited symptoms and local and/or general adverse events occurring during a 7 days post-vaccination period, and any unsolicited symptoms occurring during a 21 days post-vaccination period will be recorded on the diary card. The subjects will be instructed to contact the investigator or their delegates immediately if symptoms should manifest or in case of any signs or symptoms occurring which the subject perceives as serious.
- (4) Record concomitant medication(s)/vaccine(s) taken since the previous visit and during vaccination period.

- (5) Record and report adverse or serious adverse event if any one has occurred since the previous visit.

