### 5.3. Visit 2a (Day 3± 1) – CPK Monitoring

Creatine kinase (CPK) monitoring will be performed in 10 subjects in Part I for 1st vaccination on Day 3 with an allowed a time window of 1 day. Whole blood sample for CPK test will be collected and analyzed by local laboratory.

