### 5.4. Visit 3 (Day 14+3) – Safety screening

A safety screening will be conducted for second vaccination on Day 14 with an allowed delay of 3 days. The following study procedures should be performed in this visit.

- (1) Check withdrawal criteria.
- (2) Check contraindications to second vaccination.
- (3) Conduct a complete physical examination with an exception of body height. Measure and record the oral temperature.
- (4) Collect approximately 8 ml of whole blood sample for following local laboratory tests.
  - Hematological tests: the same as screening visit
  - Biochemistry tests: the same as screening visit

\* Re-test may be conducted 1 week later (see [Section 4.3.2](#)).
- (5) Record concomitant medication(s)/vaccine(s) taken since the previous visit.
- (6) Record and report adverse or serious adverse event if any one has occurred since the previous visit.

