## **5.6. Visit 4a (Day 24± 3) – CPK Monitoring**

Creatine kinase (CPK) monitoring will be performed in 10 subjects in Part I for 2nd vaccination on Day 24 with an allowed a time window of 3 day. Whole blood sample for CPK test will be collected and analyzed by local laboratory.

Whether Visit 2a and Visit 4a should be conducted again in Part II based on the Part I results and judged by DSMB.

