### **7.3.3. Selected laboratory safety tests**

Fasting blood samples will be collected for hematological and biochemistry examinations at Visit 1, Visit 3 and Visit 5. These tests will be conducted by local laboratory in each center.

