### 10.4.1. Variables

The secondary endpoints include:

- (1) Observed variables from baseline at a 5- $\mu$ g and 10- $\mu$ g dose on Day 21 and 42:
  - Serum IgG titers
  - Serum neutralizing antibody titers
  - Epitope mapping (only on Day 42)

The immunogenicity parameters include serum IgG titers and neutralizing antibody titers on baseline, Day 21 and Day 42, and immune epitope mapping of EV71vac will be conducted on baseline and Day 42.

The serum IgG and neutralizing antibody titers on baseline, Day 21 and Day 42 will be summarized descriptively and the change from baseline will be tested by paired T-test or

Wilcoxon signed rank test under significance level 0.05. The results of immune epitope mapping will be summarized descriptively as well.

(2) The change in the laboratory results:

- Hematology
- Biochemistry

The analysis of laboratory includes hematology and biochemistry.

Hematology tests include CBC, such as Hb, Hct, RBC count, WBC count, WBC differential and platelet count; and biochemistry tests include ALT, AST,  $\gamma$ GT, alkaline phosphatase, total bilirubin, total protein, albumin, CPK, BUN, creatinine, uric acid, total cholesterol, triglyceride and glucose (fasting).

The descriptive summary results of laboratory for the baseline, each study visit, end of visit, the change from baseline to end of visit will be presented and paired T-test or Wilcoxon signed rank test will be used to test change from baseline under significance level 0.05.

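### Section 10.4.1 tests CPK for change from baseline, but CPK is scheduled only after dosing, so no such change can be computed for any subject

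*Protocol*

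**What the plan says.** **Analysis.** Protocol 10.4.1 treats laboratory change as a secondary endpoint. Its biochemistry list includes CPK: "total bilirubin, total protein, albumin, CPK, BUN, creatinine, uric acid, total cholesterol, triglyceride and glucose (fasting". For the laboratory tests it asks for summaries at baseline, at each study visit and at the end of visit. It adds that the change "will be presented and paired T-test or Wilcoxon signed rank test will be used to test change from baseline", at level 0.05.

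**Collection.** The screening panel in 5.1 runs "total bilirubin, total protein, albumin, BUN, creatinine, uric acid, total cholesterol, triglyceride and glucose (fasting", without CPK. Table 5-1 footnote 4 and section 7.3.3.2 list the same analytes, also without CPK. Section 7.3.3 fixes the timing of the routine safety panel: "Fasting blood samples will be collected for hematological and biochemistry examinations at Visit 1, Visit 3 and Visit 5". Visit 3 is defined by reference to screening ("Biochemistry tests: the same as screening visit"), and Visit 5 in 5.7.1 likewise. Blood taken before the first dose has another purpose: "Collect approximately 7 ml of whole blood sample for following central laboratory tests", which 5.2 specifies as immunogenicity tests. The Visit 4 sample before dose 2 (5.5) is also for immunogenicity.

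**CPK itself.** Section 5.3 provides for it after dose 1: "Creatine kinase (CPK) monitoring will be performed in 10 subjects in Part I". Section 5.6 does the same for dose 2: "Whole blood sample for CPK test will be collected and analyzed by local laboratory". The footnote to Table 5-1 leaves CPK in Part II to the DSMB.

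**The concern.** The analysis section asks for a comparison that the visit schedule cannot supply. A statistical analysis plan could drop CPK from the test, but it cannot create a sample that was never drawn, and 10.5 provides no method for missing data. Once dose 1 is given, a pre-dose value cannot be recovered.

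The consequence goes a little beyond one empty table row. The trial has no control arm, and Part I enters subjects in steps of 1, 2 and 7. The sponsor thought CPK worth two dedicated visits, and the DSMB must decide from these values whether to continue CPK monitoring in Part II. Without a pre-dose value, a raised Day 3 result cannot be told apart from a subject's usual level, which weakens attribution to the vaccine.

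**Working it through.** There is no stated figure to reproduce, since 10.6 gives sample size and power as not applicable. The check is a count of scheduled CPK samples by visit, from sections 5.1 to 5.7.1 and Table 5-1.

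| Visit | Blood planned | CPK |
|---|---|---|
| 1 (Day -7 to 0) | safety panel | no |
| 2 (Day 0, before dose 1) | immunogenicity | no |
| 2a (Day 2 to 4) | CPK, Part I | yes |
| 3 (Day 14 to 17) | safety panel as at screening | no |
| 4 (Day 21 to 24, before dose 2) | immunogenicity | no |
| 4a (Day 24 to 27) | CPK, Part I | yes |
| 5 (Day 39 to 45) | safety panel as at screening, plus immunogenicity | no |

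**Samples.** Part I has 10 subjects × 2 visits = 20 scheduled CPK values, all after dose 1.

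**Computable changes as written.** Baseline to Visit 2a: 0 of 10. Baseline to Visit 4a: 0 of 10. Together 0 of 20. The change that 10.4.1 says will be presented runs from baseline to the end of visit. For CPK both ends are missing, because Visit 5 has none either. If the DSMB extends Visits 2a and 4a to Part II, the count is still 0 of 60 subjects.

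**Visit 4a window.** The heading of 5.6 gives ±3 days, while Tables 5-1 and 5-2 give +3. With ±3 and a delayed second dose, a Visit 4a sample could precede dose 2. It would still follow dose 1, so it would not be a baseline.

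**With a screening CPK.** Up to 10 + 10 = 20 of 20 changes become computable. The interval from screening to Visit 2a would be 2 - 0 = 2 days to 4 + 7 = 11 days.

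**What a test could then show.** By Table 6-1, Part I has 1 + 1 + 3 = 5 subjects in A05 and 1 + 4 = 5 in B10. The smallest two-sided exact Wilcoxon signed rank p, without ties, is 2/2^n:

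- n = 5: 2/32 = 0.0625, which cannot reach 0.05 in either dose group.
- n = 10, pooled: 2/1024 = 0.002.

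The paired t-test has no such floor, but at n = 5 the 95% interval for the mean change has a half-width of 1.24 standard deviations of the change (0.72 at n = 10). The gain from a baseline is therefore mainly descriptive.

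**The case against.** The best case on the other side is that 10.4.1 is the outlier. CPK appears in no routine panel list and is not named in the endpoint text of 9.2. No primary endpoint or stopping rule depends on a CPK change. Table 5-1 places CPK in the biochemistry row at Visits 2a and 4a, so summarising it at those visits works, and only the baseline and change clauses fail. One line in 10.4.1 would remove the contradiction. This stands, and it keeps the weight low. It does not make the stated analysis possible.

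A reader might infer more than the documents support:

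- **That a raised Visit 2a CPK leaves the subject unprotected at dose 2.** There is no scheduled repeat, and the laboratory contraindication in 4.3.2 refers to Visit 3 results. But 3.1 requires ongoing investigator review. Withdrawal criterion (4) is checked at Visit 3 and again before dose 2. A value that the investigator judges significant becomes an adverse event and is followed until it resolves or is stable (7.3.5, 7.3.5.2). The DSMB oversees safety, and nothing forbids an unscheduled repeat. A new dose-2 rule would largely restate this.
- **That post-dose CPK can be read only against the laboratory range.** Visits 2a and 4a can be compared within a subject, and A05 can be compared with B10, with 9 of the 10 Part I subjects randomised. These comparisons are weak, but they exist.

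**Conclusion.** The contradiction is real and follows from the document alone. Section 10.4.1 requires a CPK baseline and a change from it, and the schedule provides neither a pre-dose value nor a Visit 5 value. No CPK change from baseline can be computed for any subject. Post-dose values can be read against the laboratory range, against the subject's other post-dose value, or between groups of 5, but not against the subject's own pre-dose level.

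The weight is minor: one analyte, 10 subjects unless the DSMB extends the monitoring, and clinical safeguards already in place. The protocol gives no CPK event rate and none is assumed here. The conclusion assumes that sites collect what sections 5.1 to 5.7.1 list and nothing more. The documents do not support the stronger reading that dose-2 safety is uncontrolled or that a CPK at Visit 3 is required.

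**What to change.** Before enrolment, for Part I subjects, and for Part II if the DSMB keeps CPK:

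1. Add CPK to the 8 ml Visit 1 sample already drawn. Word it as *plus CPK at Visit 1*. Visits 3 and 5 are defined by reference to screening, so editing the 5.1 list alone would change them too.
2. Name this value the CPK baseline, and state that it excludes under criterion (8) of 4.2.2 only if clinically significant. Criterion (8) as worded covers any abnormal result, while 7.3.3.2 speaks of significant ones; the addition should follow 7.3.3.2.
3. In 10.4.1, define the CPK change as baseline to Visit 2a and baseline to Visit 4a, presented descriptively with individual values.

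If no baseline is added, 10.4.1 must at least restrict CPK to post-dose summaries at Visits 2a and 4a. That removes the contradiction but gives no reference.

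A Visit 3 CPK is optional. If it is added, 4.3.2(1) must say that only a clinically significant CPK is a contraindication, and must allow a re-test. The present re-test note covers only ALT/AST and creatinine, so a trivial rise could otherwise bar dose 2.

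**Cost.** Amendment wording and about 10 × 1 = 10 assays in Part I, plus a few for screen failures; up to 50 × 1 = 50 more only if CPK continues in Part II. No new visit or blood draw is needed. The limit is that a value taken 2 to 11 days before Visit 2a is a reference, not proof of cause.

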#### 4.2.2. Main exclusion criteria:

Subjects will be excluded from the study for any of the following reasons:

(1) Female who is pregnant/lactating or planning to be pregnant, or female of childbearing potential\* who is not using medically recognized method of contraception\*\*.

\* Other than those who have been surgically sterilized (defined as having undergone hysterectomy or bilateral oophorectomy or bilateral salpingectomy; tubal ligation alone is not considered sufficient) or one year post-menopausal.

\*\* Recognized contraceptive precautions, including intrauterine contraceptive device; oral contraceptives; diaphragm or condom in combination with contraceptive jelly, cream or foam; Norplant® or DepoProvera®, should be conducted until 2 months after completion of the vaccination series.

(2) Subject with body mass index (BMI) > 35.

(3) Subject with fever defined as oral temperature  $\geq 37.5^{\circ}\text{C}$  at the time of planned vaccination.

(4) Subject with previous known or potential exposure to Enterovirus 71 (EV71).

(5) Subject with a history of herpangina, hand-foot-mouth disease, acute hemorrhagic conjunctivitis or acute gastrointestinal illness associated with enterovirus infection in the past 3 months.

(6) Subject with any confirmed or suspected abnormal immune function, immunosuppressive or immunodeficient condition.

(7) Subject who has been diagnosed with a significant neurological, pulmonary, cardiovascular, hematological, hepatic or renal disorder.

(8) Subject with any abnormal laboratory results at screening.

(9) Subject with a history of hypersensitivity to vaccines, or a history of allergic disease or reactions likely to be exacerbated by any component of the vaccine.

(10) Use of any investigational/non-registered product (including drug, vaccine and invasive medical device) within 30 days prior to vaccination or planned use during the study period.

(11) Administration of any licensed vaccine within 30 days prior to vaccination or planned administration during study period (until 30 days after the second vaccination).

(12) Use of immunoglobulins or any blood products within 3 months prior to vaccination or planned use during the study period (until 30 days after the second vaccination).

(13) Chronic administration (defined as > 14 days) of immunosuppressants or other immunomodulators within 6 months prior to vaccination or planned use during the study period (until 30 days after the second vaccination).

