#### **7.3.3.1 Hematological examination**

The complete blood count (CBC) test includes hemoglobin (Hb), hematocrit (Hct), red blood cells (RBC) count, white blood cells (WBC) count, WBC differential and platelet counts.

Subjects with any significant hematologic abnormality at screening (Visit 1) will not be recruited into this study, and those with any significant abnormality at interim safety screening (Visit 3) should not receive 2nd vaccination.

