#### **7.3.3.2 Biochemistry examinations**

Biochemistry examinations include alanine transferase (ALT), aspartate transferase (AST), γGT, alkaline phosphatase, total bilirubin, total protein, albumin, BUN, creatinine, uric acid, total cholesterol, triglyceride and fasting plasma glucose (FPG).

Subjects with any significant biochemistry abnormality at screening (Visit 1) will not be recruited into this study, and those with any significant abnormality at interim safety screening (Visit 3) should not receive 2nd vaccination. However, if the level of ALT/AST or creatinine is less than 2.5 x ULN, the test could be conducted again 1 week later and the 2nd dose of EV71 vaccine will be administrated in those with normal results after that.

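### The screening laboratory sample is both entry gate and baseline, so regression to the mean can create within-group changes in analytes cut mainly at one limit; the paired-test p-values should not be read as vaccine effects

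*Protocol*

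**What the plan says.** Section 10.4.1 of the Protocol, under the change in laboratory results, plans descriptive summaries and a within-subject test: "paired T-test or Wilcoxon signed rank test will be used to test change from baseline under significance level 0.05". This is a named secondary endpoint (section 9.2).

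Section 7.3.3 fixes the sampling: "Fasting blood samples will be collected for hematological and biochemistry examinations at Visit 1, Visit 3 and Visit 5". At Visit 2, before the first dose, section 5.2 takes blood only for the central laboratory: "Immunogenicity tests: IgG and neutralizing antibody titers, and epitope mapping". The flow chart labels Visit 2 as baseline, but no safety panel is drawn there. Section 7.1 collects baseline characteristics at screening, and section 10.2 counts laboratory variables among them. Visit 1 is therefore the laboratory baseline.

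The same sample decides entry. Exclusion criterion 8 in section 4.2.2 excludes a "Subject with any abnormal laboratory results at screening". Sections 7.3.3.1 and 7.3.3.2 word the gate more loosely: "Subjects with any significant hematologic abnormality at screening (Visit 1) will not be recruited into this study", and likewise "Subjects with any significant biochemistry abnormality at screening (Visit 1) will not be recruited into this study".

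The synopsis describes the study as uncontrolled. CPK stands apart: section 10.4.1 lists it among the tested variables, but the screening panel in section 5.1 does not include it, and it is first measured after vaccination, at Visit 2a.

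**The concern.** A baseline that had to pass a limit is, on average, too far from that limit. At the next draw, part of the favourable chance variation at screening disappears and the group mean moves back toward the limit. A paired test attributes that movement to whatever happened between the two draws, which here is vaccination. This is bias, not chance, so a multiplicity adjustment would not remove it. With both arms vaccinated, nothing in the within-group test separates it from a vaccine effect. For analytes where the upper limit is the one that matters, the spurious movement is upward, the direction a reader would take for toxicity.

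At stake is how the laboratory secondary endpoint of a first-in-human safety study is read.

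**Working it through.** **The plan's own figures.** Section 10.6 gives no sample-size or power derivation, so there is none to reproduce. Table 6-1 adds up as stated: A05 has 1 + 1 + 3 + 25 = 30 subjects and B10 has 1 + 4 + 25 = 30, in total 60.

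**Inputs from the Protocol.** Significance level 0.05 (section 10.4.1; sidedness is not stated, two-sided assumed); n = 60 pooled or 30 per dose; Visit 1 as gate and baseline.

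**Assumed inputs, which the Protocol does not give.** The share u of candidates above an analyte's upper limit, and the correlation ρ between visits within a person. Values are taken as normal and standardised, with no vaccine effect, no dropout and no further selection at Visit 3.

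**Expected spurious change.** If Visit 1 is truncated above at z = z(1−u), the mean of the admitted baselines is −φ(z)/(1−u) SD and the later mean is ρ times that. The expected change is

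(1−ρ) · φ(z)/(1−u) SD, in SDs of the unselected candidates.

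At ρ = 0.7:
- u = 2.5%: 0.3 × 0.0584/0.975 = 0.018 SD
- u = 10%: 0.3 × 0.1755/0.90 = 0.058 SD
- u = 20%: 0.3 × 0.2800/0.80 = 0.105 SD

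**Check of the simulation.** Without selection, the two-sided paired t-test rejects in 0.047 (n = 30) and 0.051 (n = 60) of simulated trials, so it is nominal.

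**Rejection rate with a one-sided cut and no vaccine effect.** For u = 10% and 20%, 8,000 trials per setting, shown for ρ = 0.6 / 0.7 / 0.8:

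| Share above limit | n = 60 | n = 30 |
|---|---|---|
| 2.5% | 0.050 to 0.054 | 0.048 at ρ = 0.7 |
| 10% | 0.100 / 0.083 / 0.075 | 0.076 / 0.069 / 0.062 |
| 20% | 0.231 / 0.189 / 0.137 | 0.138 / 0.112 / 0.092 |

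Nearly all rejections are upward: with u = 20%, ρ = 0.6 and n = 60, 0.235 in an independent rerun, against a nominal 0.025 in that tail.

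**Counter-check, symmetric cuts.** With 2.5% or 10% removed at each end, n = 60 and ρ from 0.5 to 0.9, the mean change is 0.00 SD and the rejection rate is 0.050 to 0.051.

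**Newly abnormal values.** With symmetric 2.5% tails, the chance that a value normal at Visit 1 is abnormal at a later draw is 4.3%, 3.5% and 2.1% for ρ = 0.5, 0.7 and 0.9. Unselected volunteers would show 5% at any draw.

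**Comparison between doses.** Both groups pass the same gate, so with no vaccine effect each has the same expected change (0.105 SD at u = 20%, ρ = 0.7). The difference is 0.105 − 0.105 = 0.

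**The case against.** The strongest reply is that a material effect cannot be shown from the Protocol. It gives neither the share of candidates above any limit nor the within-person correlation, and at a conventional 2.5% share the test is essentially nominal. The endpoints are stated by dose, so n = 30 is relevant, and there the inflation is smaller. No stated decision uses these p-values: Part II depends on the DSMB's safety review, the suspension criteria in section 8.4 are clinical, and section 7.3.5 leaves laboratory adverse events to the investigator's judgement or the need for treatment. All of this stands. It limits the size and the consequence, but it does not make the test valid.

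Four stronger readings are tempting, and the documents do not support them.
- A reader might infer that laboratory means in general will rise. They shift only where the cut is asymmetric, and a cut mainly at the lower limit would give a fall.
- A reader might infer that every shift must run from normal to abnormal. That needs the strict wording of criterion 8; under sections 7.3.3.1 and 7.3.3.2 mildly abnormal values can enter.
- A reader might infer that the gate creates an excess of newly abnormal values. The later share is below the 5% expected without selection, and no laboratory shift table is planned.
- A reader might infer that a new Day 0 baseline sample is needed. It would remove the bias only if Visit 1 correlates equally with Visit 2 and with later visits. Screening may be at most 7 days before dosing. With assumed correlations of 0.95 (Visits 1 and 2) and 0.70 (Visits 1 and 5), and 20% above the limit, (0.95 − 0.70) × 0.350 = 0.0875 SD of the 0.105 SD would remain, at the price of 60 extra panels.

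**Conclusion.** The concern holds in limited form. For haematology and biochemistry other than CPK, one sample serves as entry gate and as the only possible baseline, and the within-group test in section 10.4.1 cannot distinguish regression to the mean from a vaccine effect. The spurious mean change arises in analytes cut mainly at one limit. Its size cannot be determined from the Protocol: across the assumed range it runs from negligible (about 5% rejection) to 14-23% at n = 60, or 9-14% at n = 30, when 20% of candidates exceed the limit. These figures rest on normal values, correlations of 0.6 to 0.8 and the strict gate. If only significant abnormalities exclude, the bias is smaller. Criterion 8 and sections 7.3.3.1 and 7.3.3.2 disagree on which rule applies and must be reconciled. CPK lies outside this point: without a pre-vaccination value, its change from baseline cannot be tested at all.

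**What to change.** Change the analysis wording in section 10.4.1 only:
- Present within-group laboratory change descriptively, as mean change with SD or an interval. State that the baseline values were subject to the entry rule, because an interval carries the same bias as the test.
- Do not use the paired t-test or Wilcoxon p-value as evidence of a vaccine effect.
- If a test is wanted, compare 10 µg with 5 µg at Visits 3 and 5 with adjustment for the screening value. Restrict it to the randomised subjects, which leaves out the single Block A subject who is assigned to A05 by rule: 29 against 30 if all are followed.
- Reconcile exclusion criterion 8 with sections 7.3.3.1 and 7.3.3.2, so that the selection behind the baseline is defined.

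The cost is a few sentences; no new blood sample is required. The downside is that an effect equal at both doses is not tested. The dose comparison is also exploratory and unpowered, and should be labelled so.

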### 10.3.2. Statistical hypothesis, model, and method of analysis

No specific hypothesis is planned to be performed. The main objective is to assess the incidence rate of adverse events. All results will be presented using descriptive statistics.

All solicited and unsolicited adverse events during the study period will be record and analyzed. Adverse events will be coded with MedDRA coding system and will be summarized by system of organ and preferred term. The percentage of subjects with adverse event (solicited and unsolicited) will be tabulated with count, percentage and 95% confidence Interval for each vaccine dose and overall results. The severity and relationship to study medication of adverse events will be summarized as well.

The incidence of serious adverse events will also be summarized; furthermore, the brief summary about serious adverse event will be presented.

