#### **10.4.2. Safety**

The evaluated variables for safety include vital signs and physical examination.

(1) Vital signs

The summary of vital signs includes systolic/diastolic blood pressure, heart rate and body temperature. The descriptive summary results for the baseline, each study visit, and end of visit, the change from baseline to end of visit will be presented, and paired T-test or Wilcoxon signed rank test will be used to test change from baseline under significance level 0.05.

(2) Physical examination

The physical examination will be summarized descriptively by visit. Besides, the transition state of physical examination from baseline to end of visit will be summarized as well.

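### Laboratory and vital-sign safety rests on many unadjusted 0.05 tests of mean change, which yield chance findings and do not count the subjects who move out of range

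*Protocol*

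**What the plan says.** Protocol 10.4.1(2) makes change in haematology and biochemistry a secondary endpoint. It plans descriptive summaries at baseline, each visit and the end, and adds that a paired t-test or "Wilcoxon signed rank test will be used to test change from baseline under significance level 0.05". Synopsis X.4(5) says the same for laboratory parameters. For vital signs, 10.4.2(1) states: "the change from baseline to end of visit will be presented, and paired T-test or Wilcoxon signed rank test will be used", again at 0.05. None of these places adjusts for multiplicity, calls the tests exploratory, or says whether they are run within each dose group or on both groups together.

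The variables tested are:
- Haematology (10.4.1): "Hematology tests include CBC, such as Hb, Hct, RBC count, WBC count, WBC differential and platelet count".
- Biochemistry (10.4.1): 14 analytes, ending "albumin, CPK, BUN, creatinine, uric acid, total cholesterol, triglyceride and glucose (fasting".
- Vital signs (10.4.2): "The summary of vital signs includes systolic/diastolic blood pressure, heart rate and body temperature".

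The procedures do not match this list. The screening panel in 5.1 runs "total bilirubin, total protein, albumin, BUN, creatinine, uric acid, total cholesterol, triglyceride and glucose (fasting", which has 13 analytes and no CPK. Section 5.3 says "Creatine kinase (CPK) monitoring will be performed in 10 subjects in Part I" after the first vaccination, and 5.6 says the same for the second, so CPK has no pre-vaccination value. No visit procedure or schedule row includes blood pressure or heart rate; oral temperature is the only vital sign collected.

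For the primary safety objective, 10.3.2 plans no hypothesis: "All results will be presented using descriptive statistics".

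**The concern.** The trial is uncontrolled and gives about 30 subjects each dose. The laboratory safety question is whether individual subjects developed abnormal values, and how many at each dose. A test of zero mean change does not answer that. It can produce nominally significant shifts by chance, and without a control arm even a true within-group shift cannot be attributed to the vaccine. It can also stay silent when one subject has a large rise. At stake is how the laboratory tables are read: a few asterisks may be taken as signals, or their absence as reassurance, when neither reading is justified.

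**Working it through.** The protocol gives no test count and no error rate to reproduce (10.6 is marked not applicable), so the count is built from its lists.

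**Number of tests**
- Haematology: 5 named variables plus the differential. The number of differential components is not given; taken as 1 to 5, the total is 6 to 10.
- Biochemistry: 14 listed, 13 with a baseline.
- Vital signs: 4 listed, 1 scheduled.
- Dose groups: 2, with 30 subjects each from Table 6-1 (1+1+3+25 and 1+4+25).

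Expected chance findings = 0.05 × k if every null is true. The chance of at least one = 1 − 0.95^k if the tests are independent.

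| Reading | k | Expected | At least one |
|---|---|---|---|
| Per dose, scheduled data, differential as 1 | 2×(6+13+1) = 40 | 2.0 | 87% |
| Per dose, scheduled data, differential as 5 | 2×(10+13+1) = 48 | 2.4 | 91% |
| Per dose, every listed variable | 2×(10+14+4) = 56 | 2.8 | 94% |
| Pooled, lowest count | 20 | 1.0 | 64% |
| Pooled, every listed variable | 28 | 1.4 | 76% |
| Per dose, every listed variable, two post-baseline visits | 112 | 5.6 | 99.7% |

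Correlation between analytes leaves the expected number unchanged but alters the last column and widens the spread. Under independence the chance of exactly 2 or 3 is 46% at k = 40, 48% at k = 48 and 47% at k = 56.

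**One marked abnormality among 30**

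These values are illustrative assumptions, not protocol figures: the changes have mean 0 and SD 6, and one subject has a further +120. Then approximately:
- mean = 120/30 = 4;
- variance = 36 + 120²×(29/30)/29 = 36 + 480 = 516, so SD = 22.7;
- standard error = 22.7/√30 = 4.15, so t = 4/4.15 = 0.96.

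As the outlier X grows, the mean tends to X/30 and so does the standard error, so t tends to 1 however large the rise. With 29 degrees of freedom that is a two-sided p of about 0.33.

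Simulation agrees. In two sets of 4,000 runs at +120, the t-test rejected in 0.0% and the Wilcoxon test in 5.3% and 4.6%; with no outlier the rates were 4.8% and 5.1%. With two such subjects the t-test rejected in 0.1% and 0.0%, the Wilcoxon in 7.3% and 7.0%. Varying one subject's rise from +50 to +400 gave at most 1.8% for the t-test and 4.2% to 5.8% for the Wilcoxon.

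**Timing of other checks**

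The second dose falls on Day 21 to 24. The scheduled DSMB review is 14 days after Block C's second vaccination, so Day 35 to 38. Visit 5 opens on Day 39. Block C's Visit 5 laboratory results therefore cannot be in that review, and Visit 5 is the only full laboratory panel after the second dose.

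**The case against.** The best defence is that the paired test was never meant to find individual abnormalities, because other provisions do that.
- Synopsis X.4(2) reports median and range, so an extreme value would show as the maximum.
- Section 4.3.2 checks each subject's laboratory results at Visit 3.
- Section 7.3.5 records a laboratory change as an adverse event if it needs treatment or the investigator so judges, and it then enters the primary analysis with counts and confidence intervals.
- The DSMB reviews each Part I subject.

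A reader might therefore infer that the plan as a whole misses marked abnormalities, or summarises mean change alone. The documents do not support either inference. What remains is that none of these provisions gives the number of affected subjects by dose. A range shows one extreme, without that subject's baseline. The adverse-event route depends on judgement, and no rule screens individual results at Visit 5.

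A reader might also see a contradiction with the statement in 10.3.2 that results are descriptive. That section governs the primary objective, while laboratory change is a secondary endpoint, so the two do not conflict.

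Three further points have force. Shift tables may sit in a statistical analysis plan, so their absence from the protocol is not itself an error; the point here is the test that the protocol does fix. Exclusion criterion 8 bars abnormal screening results, so a shift table may reduce to nearly one row, but that row still holds the missing count. Finally, no p-value drives a decision, since the stopping criteria and the start of Part II are event-based. That limits the harm, and it also means that little is lost by removing the tests.

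**Conclusion.** The concern holds in a limited form. The protocol fixes a method that suits its laboratory and vital-sign safety data badly. If tests are run per dose at one time point, about 2 to 3 nominally significant changes are expected when nothing truly changes; if pooled, 1.0 to 1.4. This rests on every null being true and on the assumed differential count, grouping and visit. The figure of 56 is a construction from the lists, not a protocol figure, and not all 56 tests can be run. Nor does an expectation of 2 to 3 mean that exactly that many will appear. The finding that a single marked rise goes undetected uses assumed values, though the limit of t at 1 does not depend on them. The consequence is for interpretation and reporting; no decision in the trial turns on these tests.

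**What to change.** In synopsis X.4(5), 10.4.1(2) and 10.4.2(1), drop the 0.05 tests for laboratory and vital-sign change. At minimum, label them exploratory and state the group and visit for each.

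Keep the descriptive summaries of change. Mark any confidence intervals as descriptive and unadjusted, because unadjusted 95% intervals would exclude zero by chance as often as the tests reject.

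For laboratory values, report by dose and visit the number of subjects below, within and above the normal range, from baseline to worst post-dose value, with a listing of out-of-range subjects.

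Reconcile the analysis list with the schedule: CPK has no baseline, and blood pressure and heart rate are analysed but not scheduled.

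The new tables use data already collected. The cost is a few extra tables and the loss of p-values that support no decision.
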